### Sample size calculation

For the primary outcome (weight), we have calculated in G*Power that we need to recruit 100 families in each study arm, based on two-sided testing with alpha of 5%, and assuming 20% drop out in order to have at least 80% power to detect a 2 kg difference in weight gain/retention between intervention arms. This is based on the intervention effect on gestational weight gain of the DALI intervention (Simmons D: JCEM 2016), and assuming non-significant clustering in weight within HPs. With this sample size, a 0.45 (SD 1.0) difference in birthweight z-score or infant BMI z-score can be found with 80% power. Since both trials will initially be analyzed separately and assuming non-significant clustering in weight within HPs, clustering by country (Germany, Austria) is not considered in the sample size calculation. Based on previous exchange with HPs, we estimated 2-4 families per HP as realistic. Therefore we intend to recruit at least 60 HPs in each study arm.

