### Statistical analyses

In multilevel analyses, we will assess whether the clustered nature of the data (individuals clustered within families and HPs) has an effect on the results. If present, the impact of the intervention on the primary outcome and secondary outcomes will be analyzed using multi-level-models. If not, linear regression analysis will be used. Analyses of intervention effects will be based on the intention-to-treat principle. Given the cluster randomized design of the study, analyses on intervention effects will be adjusted for baseline values of the outcome. If suitable, missing data will be checked for randomness and be imputed using multiple imputations. Furthermore, we plan to assess the influence of moderating (stressful life events, parent child interaction, social support, partnership quality) and mediating (emotion regulation, self-efficacy) variables to identify determinants and pathways for the intervention’s efficacy and unhealthy weight gain during pregnancy and postpartum.

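### The power statement for this HP-randomised trial contains no design effect, so its 80% has almost no allowance for clustering within HPs

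*Protocol article*

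**What the plan says.** The Randomization section of the protocol article makes the HP the unit of randomisation. The Sample size calculation section then states that "we need to recruit 100 families in each study arm", using two-sided testing at 5% and 20% dropout, to have "at least 80% power to detect a 2 kg difference in weight gain/retention between intervention arms". It does so "and assuming non-significant clustering in weight within HPs". It gives no ICC, no design effect and no SD for the 2 kg difference. The one effect given with an SD is a companion figure: "a 0.45 (SD 1.0) difference in birthweight z-score or infant BMI z-score can be found with 80% power".

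On cluster numbers, the same section says "we estimated 2-4 families per HP as realistic. Therefore we intend to recruit at least 60 HPs in each study arm". The abstract gives N = 400 over the two trials, and the section says they are initially analysed separately. So 100 per arm is the figure for each trial (2 trials x 2 arms x 100 = 400).

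For the analysis, the Statistical analyses section says "we will assess whether the clustered nature of the data (individuals clustered within families and HPs) has an effect on the results". Multilevel models are used if it does, and linear regression otherwise.

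**The concern.** Power in a cluster trial depends on the size of the ICC and on the number of families per HP. It does not depend on whether a test would find the clustering significant. With only a few families per HP, such a test would itself have little power, so a non-significant result says little about how large the ICC is. Some correlation is plausible here, because the same HP recruits the families and delivers the counselling.

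If the calculation has no allowance for clustering, the 80% is optimistic by an amount the article does not let the reader judge. A null result would then be read against a power figure that ignores the design.

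The HP target raises a separate question. The text presents 60 HPs per arm as following from 2-4 families per HP, but the link to 100 families per arm is not clear.

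**Working it through.** **Inputs from the protocol article:** two-sided alpha 0.05; 100 families per arm; 20% dropout, so 100 x 0.8 = 80 analysed; 0.45 with SD 1.0 for the z-scores; 2 kg for weight, without an SD; 2-4 families per HP; at least 60 HPs per arm. **Assumed, because the article gives no value:** ICC 0.01, 0.05 and 0.10.

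**Step 1: the plan's own figure.** For a two-sample t-test (noncentral t) with d = 0.45, 79 analysed families per arm are needed, and 79 / 0.8 = 98.75, so 99 recruited. The normal approximation gives 78 and 98. The stated 100 per arm therefore reproduces, but with individual randomisation and no design effect. Power at 80 per arm is 80.8%.

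**Step 2: the margin.** Exactly 80% power for d = 0.45 needs 78.49 per arm. The largest tolerable design effect is 80 / 78.49 = 1.019.

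**Step 3: the SD behind 2 kg.** With 80 per arm, 80% power needs d = 0.4457, so the SD can be at most 2 / 0.4457 = 4.49 kg if the claim is to hold under independence. At SD 4.0 kg power would be 88.2% before clustering.

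**Step 4: clustering.** Design effect DE = 1 + (m - 1) x ICC, with m the analysed families per HP and effective n = 80 / DE. After dropout, 2-4 recruited per HP become m = 2 x 0.8 = 1.6 to 4 x 0.8 = 3.2. The detectable difference is close to 2 kg x sqrt(DE).

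| m | ICC | DE | Effective n per arm | Power, 0.45 (SD 1.0) | Power, 2 kg at SD 4.49 | Detectable at 80%, SD 4.49 |
|---|---|---|---|---|---|---|
| 1.6 | 0.01 | 1.006 | 79.5 | 80.5% | 79.8% | 2.01 kg |
| 1.6 | 0.05 | 1.03 | 77.7 | 79.6% | 78.8% | 2.03 kg |
| 1.6 | 0.10 | 1.06 | 75.5 | 78.4% | 77.6% | 2.06 kg |
| 3.2 | 0.01 | 1.022 | 78.3 | 79.9% | 79.1% | 2.02 kg |
| 3.2 | 0.05 | 1.11 | 72.1 | 76.5% | 75.7% | 2.11 kg |
| 3.2 | 0.10 | 1.22 | 65.6 | 72.5% | 71.7% | 2.21 kg |

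The z-score effect keeps 80% power up to an ICC of 0.0192 / 0.6 = 0.032 at m = 1.6, and 0.0192 / 2.2 = 0.009 at m = 3.2.

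**Step 5: the HP target.** 60 HPs x 2-4 families = 120-240 families.
- If 60 is per arm in each trial: 100 / 60 = 1.67 families per HP, below the stated range.
- If 60 is per arm over both trials: 200 / 60 = 3.33 families per HP, inside the range.

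After dropout these are 1.67 x 0.8 = 1.33 and 3.33 x 0.8 = 2.67 analysed. The first reading gives the smaller design effect: at ICC 0.05, 1 + 0.33 x 0.05 = 1.017 against 1 + 1.67 x 0.05 = 1.083.

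**The case against.** The strongest reply is that little is lost and that the loss may be nil for the primary outcome. The clusters are very small, the claim is worded as a minimum, and the weight SD is unknown. At an SD of 4.0 kg, power stays above 80% even at m = 3.2 and ICC 0.10 (80 / 1.22 = 65.6 effective, 81.1%). The analysis also plans baseline adjustment, which may recover some precision, and multilevel models where clustering shows. All the ICCs used here are assumptions. This stands, and it limits the size of the point. It does not remove it: the article states a clustering assumption and a power result that rests on it, and neither the SD nor an ICC is given to support the claim.

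Three stronger readings are tempting, and the document supports none of them.

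- A reader might infer that 80% holds only at an ICC of exactly zero. For weight, that follows only if the SD is taken to be 4.49 kg, a value obtained by solving for exactly 80%, which removes the slack by construction. The z-score figure tolerates a small positive ICC.
- A reader might infer that the HP target contradicts 100 families per arm and so costs power. Over both trials, 3.33 per HP fits the stated range. Per trial, a target of at least 60 may hold a reserve for HPs who recruit few or no families, and fewer families per HP lowers the design effect. What remains is an ambiguity.
- A reader might combine 60 HPs over both trials with 2 families each: 60 x 2 / 2 = 60 per trial arm, 60 x 0.8 = 48 analysed, and power of about 58% even without clustering. That describes a recruitment shortfall against the planned 100 families per arm. It is not the planned design.

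**Conclusion.** The point holds in a limited form. The sample size reproduces under independence, and the margin above 80% for the stated z-score effect covers a design effect of only about 1.02. Over the plan's own range of families per HP, less dropout, power for that effect is about 1 to 4 percentage points below the 80.8% obtained under independence at ICC 0.05, and about 2 to 8 points below it at ICC 0.10.

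For the 2 kg difference the position cannot be settled from the article. At the largest compatible SD, the difference detectable with 80% power rises from 2.0 kg to at most about 2.2 kg; at a smaller SD the claim may survive.

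These figures rest on assumed ICCs, equal numbers of families per HP, an effective-sample-size approximation and no credit for baseline adjustment. The uncertainty about 60 HPs per arm needs clarifying but is not itself a cause of lost power.

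**What to change.** In the Sample size calculation section:

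1. Remove the phrase about non-significant clustering and state an assumed ICC range, for example 0.01-0.10.
2. Give the SD behind the 2 kg difference.
3. Restate power, or the detectable difference, over that ICC range at the expected analysed families per HP. If baseline adjustment is counted on, state the correlation assumed.
4. Say whether 60 HPs per arm applies to each trial (1.67 families per HP) or to both together (3.33 per HP), and how it agrees with 100 families per arm, including any reserve for HPs who recruit no family.

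The cost is text only, with no extra families. The downside is a stated power that may be slightly less favourable.

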### Procedure

In *Austria,* HPs will register online and complete an online questionnaire including the consent to the study as well as questions about their professional background. After registration, they will be randomized to one of the study arms (I-PREGNO combined with TAU versus TAU only). Afterwards the study coordinator will get in contact with the HPs via telephone (onboarding). During the telephone call, the HPs will be informed about the condition they have been randomly assigned to and will receive a 20-30 minute briefing with instructions on the study materials. Before they start the recruitment of families, HPs who have been assigned to the intervention condition will receive a five-hour-online-training for the blended counseling. In a second step, the HPs will start to inform every pregnant woman, who has an appointment for the first counseling (between week 18-22 of pregnancy), and send the registration link to interested families. Interested families will also receive information material and data protection information. After the registration, families that meet the eligibility criteria will receive a link for the online baseline questionnaire (t0) from the study team, which has to be completed before the appointment with their midwife. After the families have completed the baseline assessment, the HP and participants receive a message to start the intervention phase and, in case of the intervention condition, a download guide for the app. Five weeks before birth, families receive the link for a second assessment (t0.5) via email. Eight weeks after birth, the families will receive the link for the post assessment (t1), which marks the end of the intervention. Three months after the end of the intervention, participants will be asked to complete a follow-up online questionnaire (t2). In case of non-response, participants will be reminded via email and telephone through the I-PREGNO coordination team.

In *Germany*, HPs will be able to register online and complete an online questionnaire containing the consent to the study, the screening for inclusion and exclusion criteria, as well as questions about their professional background. Eligible HPs will be randomized to one of the two study conditions, contacted via email with the information about their group assignment, and sent forms and materials by mail. Afterwards, the study coordination will get in contact with the HPs via telephone and conduct a 20-30 minutes briefing with instructions on the study materials (onboarding). If they have been assigned to the intervention condition, they will receive a five-hour online training for the blended counseling. In a second step, the HPs will screen each of their families for the eligibility criteria, inform potential families about the study, and provide information material, as well as data protection policies to interested families. HPs will be able to register families online. The participating families receive an individualized link for the baseline assessment (t0) via mail. After the families have completed the assessment, the HP and the participants receive a message to start the intervention and – in case of the intervention condition – a download guide for the app. After 12 weeks, the families receive the link for the post assessment (t1) via email. Three months after the end of the intervention, participants will be asked to complete a follow-up online questionnaire (t2). In case of non-response, participants will be reminded via email and telephone as well as through the HP. In both countries, the app access will be deactivated after the intervention period for the intervention group and (again) activated for each participant (also for the control group) after the last assessment (t2) is completed.

### Randomization

Cluster randomization was chosen to prevent contamination of the different conditions. This means that every HP should provide the same treatment to all of their families participating in the I-PREGNO study. Participating HPs will be randomly assigned to one of the two study arms and will be informed about the assignment immediately. The randomization will be performed using a computerized random number generator, pre-stratified for the two trials provided by an external, independent expert from the Department of Computing in the Cultural Sciences at the University of Bamberg.

### Interventions

#### I-PREGNO

The I-PREGNO intervention follows a blended counseling approach, combining a self-guided app for families with face-to-face counseling conducted through the HPs. The interventions will be implemented in existing healthcare structures in Germany and Austria.

The interactive self-guided modular I-PREGNO app, integrates basic principles of evidence-based cognitive-behavioral therapy (CBT) and behavior change techniques [45]. The app aims to help families to increase their mental health, to reduce psychosocial stress, and to broaden their knowledge about nutrition and physical activity topics via the completion of a variety of thematic modules. I-PREGNO was built on the technical and content-related knowledge gained from the gender-sensitive multicomponent mHealth weight loss intervention I-GENDO [46]. Both apps were developed within an iterative process by the authors working closely with an external software provider (groupXS Solutions GmbH). To address the needs of psychosocially burdened families and to adapt the existing content and approach of the intervention, we conducted focus groups with families and HPs (midwives, family midwives, health nurses, social workers).

Figure 3 provides an overview of the I-PREGNO app interface. The app consists of a modular psychological intervention (‘Module Overview’, ‘Resume’), self-monitoring of mood, exercise eating behavior, and sleep quality through a personalized diary (‘Journal’), a folder to save favorite exercises and strategies (‘Favorites’), information about the study itself and emergency contacts (‘Study Info’, ‘Quick Help’), and a selection of accompanying coaches (‘Select Coach’). One particularity is the possibility to adapt the content to the phase the user is currently in (pregnancy or postpartum; “My baby is here!”). In addition to this individual customization within the app, we provided two app releases with slightly adapted content, one for the mothers and one for the fathers to ensure that the app content fits to the different needs and perspectives. The app is available for smartphones with iOS and Android. To use all app features a study code and password is required. The core of the app, the psychological intervention, includes 12 modules that focus on improving specific psychosocial or behavioral aspects associated with gestational weight gain, retention, and perinatal mental health. Two modules address the introduction to (getting to know the app, goal setting) and one addresses the conclusion (review and relapse prevention) of the intervention program. Seven more modules focus on improving core competences for parents: self-care, stress management skills, emotion regulation skills, self-efficacy, self-esteem, mindfulness, and social competences/social support. The remaining two modules address nutrition and exercise behavior of parents. These have been created within the framework of the counseling and contain appropriate exercises and information.

**Fig. 3 Fig3:**
[figure not shown]
Interface of the App I-PREGNO

Each module consists of a various number of sessions (range: 2 - 18). To ensure autonomy, users are able to work through the modules and sessions as desired. In line with existing research [47], we recommend users to use the app at least three times a week with a duration of approximately 15 minutes to improve the targeted core competences. Each completed session is marked with a check mark and the module tracks the user’s progress. The sessions include psychoeducational information, several CBT-based self-help techniques, skill trainings (i.e., coping strategies, cognitive restructuring) and, a range of behavior change techniques (i.e., goal setting, monitoring, shaping knowledge) delivered through text, audio, images, and interactive elements that require participants’ input (e.g., filling out gap texts).

The face-to-face counseling includes guidance for health behavior change focusing on physical activity and nutrition and is delivered by the HP. It was built on principles of patient empowerment and CBT skills inspired by Motivational Interviewing [48]. The counseling is based on seven key messages (*[1]**Make water YOUR drink of choice, [2] Diversity does not have to be a lot, [3] Colorful and healthy: plant-based foods, [4] Snacks & fast food: (un)canny seducers, [5] Finding the right amount of meat, [6] Finding joy in movement and sitting less, [7] Train your strength*) that are also presented within the app. The counseling was developed together with HP so that it can easily be implemented in the existing face-to-face appointments during prenatal care and early intervention programs after birth. During the counseling, specific messages will be chosen together with the HP, depending on the knowledge as well as individual needs of the families. In our study, HPs will integrate the counseling in the appointments of TAU with their families (on average five sessions). The counseling takes about 10-15 minutes per appointment. 

The HPs in the intervention group will be trained in the I-PREGNO key messages (i.e., psychoeducation on eating and physical activity behavior) and in Motivational Interviewing techniques (i.e., ways to address the key lifestyle messages wih families, approaches to work through resistance). Sports scientists, psychologists and an ecothrophologist with further qualifications in Motivational Interviewing will deliver the training. HPs will be supervised by a Motivational Interviewing expert throughout the course of the intervention phase.

#### Treatment as usual

In both countries, both groups will receive TAU. In *Austria,* TAU represents perinatal care delivered by midwives (with usually one appointment before and up to seven appointments after birth). During the first appointment, usually scheduled at 18-22 weeks of gestation, topics such as the place of birth, nutrition and physical activity during pregnancy are discussed, as well as information on health promotion and preventive behavior. From the first to the fifth day after birth, the midwife will check on the mother and baby once a day. From the sixth day up until eight weeks after birth, women have up to seven further optional appointments with the midwife. During the appointments, medical examinations are carried out and information on health behavior (including physical activity and nutrition), and breastfeeding is provided.

TAU in *Germany* represents a long-term home-visiting program for psychosocially burdened families within the framework of early childhood intervention that usually starts during the postpartum period. The preventive and voluntary offer is particularly tailored to families who find themselves in psychosocially burdening living conditions. The service is delivered by trained HPs (family midwives, family and child nurses) and thus aims to have a low-threshold access. Regular home visits (usually weekly) are intended to provide comprehensive support regarding questions about child development or coping with everyday tasks for psychosocially burdened families with children aged between zero and three years. It is provided nationwide but with local configurations. The home-visiting program is funded by the Federal Ministry of Family Affairs, Senior Citizens, Women and Youth (BMFSFJ) as part of the Federal Foundation for Early Childhood Intervention (Bundesstiftung Fruhe Hilfen).

### Outcomes

Our primary outcome will be body composition measured through body mass index (BMI) of the family members (self-reported, the mother’s, if available father’s and the child’s height and weight). Secondary outcomes will be eating behavior (i.e., eating styles), physical activity, and psychological factors (i.e., depression, emotion regulation, parental stress) that are associated with the family’s well-being and influence eating behavior and physical activity. Information about the children (height, weight, breastfeeding) is collected through the mothers. Since the project primarily intends to reach psychosocially burdened families another focus lies on socio-demographic characteristics and socio-economic stressors (e.g., whether families receive social support, health status, crowded living conditions, and the migrant status of the parents). Data will be gathered at three (Germany) or four (Austria) time points. Tables 2 and 3 provide an overview of the included measurements.

**Table 2 Tab2:** Data collection at different time points during the study in Austria

Questionnaire	t_0_	t_0.5_	t_1_	t_2_
	18^th^ to 22^nd^ week of pregnancy	35^th^ -37^th^ week of pregnancy	8 weeks pp	3 months after t_1_
Socio-demographics	x			
Weight of the parent	x	x	x	x
Child’s weight and height			x	x
DEBQ	x	x	x	x
FFQ	x	x	x	x
IPAQ	x	x	x	x
EPDS	x	x	x	x
DERS-SF	x	x	x	x
ECR-RD		x		
GSE	x	x	x	x
CTS		x		
PSI-SF			x	x
PBQ			x	
I-FEEL				x
Regulatory Disorders				x
MAUQ			x	

*DEBQ* Dutch Eating Behaviour Questionnaire, *FFQ* Food Frequency Questionnaire, *IPAQ* International Physical Activity Questionnaire, *EPDS* Edinburgh-Postnatal-Depression-Scale, *DERS-SF* Difficulties in Emotion Regulation Scale, *ECR-RD* Experiences in Close Relationships, *GSE* General Self-Efficacy Scale, *CTS* Childhood Trauma Screener, *PSI-SF* Parenting Stress Index, *PBQ* Postpartum Bonding Questionnaire, *MAUQ* mHealth app usability questionnaire, *pp* postpartum

**Table 3 Tab3:** Data collection at different time points during the study in Germany

Questionnaire	t_0_	t_1_	t_2_
	0-12 months pp	3-15 months pp	3 months after t1
Socio-demographics	x		
Weight of the parent	x	x	x
Child’s weight and height	x	x	x
DEBQ	x	x	x
FFQ	x	x	x
IPAQ	x	x	x
EPDS	x	x	x
DERS-SF	x	x	x
ECR-RD		x	
GSE	x	x	x
CTS	x		
PSI-SF	x	x	x
PBQ	x	x	x
I-FEEL			x
Regulatory Disorders			x
MAUQ		x	

*DEBQ* Dutch Eating Behaviour Questionnaire, *FFQ* Food Frequency Questionnaire, *IPAQ* International Physical Activity Questionnaire, *EPDS* Edinburgh-Postnatal-Depression-Scale, *DERS-SF* Difficulties in Emotion Regulation Scale, *ECR-RD* Experiences in Close Relationships, *GSE* General Self-Efficacy Scale, *CTS* Childhood Trauma Screener, *PSI-SF* Parenting Stress Index, *PBQ* Postpartum Bonding Questionnaire, *MAUQ* mHealth app usability questionnaire, *pp* postpartum

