Based on the challenges during COVID-19 and the fast-evolving digital change in the last decade, an mHealth based intervention could be an effective approach to prevent unhealthy weight gain and psychosocial stress in vulnerable families during the perinatal period. The intervention should initially focus on psychological factors known to be related to health behaviors affecting the perinatal weight gain, involve both parents, and should be extended over the complete perinatal period. As first of its kind, the overall objective of I-PREGNO is the development and evaluation of an mHealth intervention that aims to prevent unhealthy weight in psychosocially burdened families through the promotion of health behavior (i.e., eating behavior and physical activity), and the parental well-being during the perinatal period. I-PREGNO was developed from June 2021 to July 2022 and consists of a self-guided multicomponent smartphone app combined with face-to-face counseling that can be implemented into existing perinatal care services. In two cluster randomized controlled trials (cRCTs) we will examine the efficacy of the intervention in existing health and family care services during pregnancy and the postpartum period. We expect that our developed mHealth intervention has a positive effect on the prevention of unhealthy weight gain (indicated by a body mass index (BMI) that is more stable than in the control condition) during the pregnancy and postpartum period and promotes psychological competences (i.e., emotion regulation, self-efficacy) that reduce stress and poor mental health particularly in vulnerable families.

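### The primary outcome is weight in the sample size section but BMI of mother, father and child in the Outcomes section, and none of the three is ranked as primary

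*Protocol article*

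**What the plan says.** Two sections of the Protocol article define the primary outcome.

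- **Sample size calculation:** "For the primary outcome (weight), we have calculated in G*Power that we need to recruit 100 families in each study arm". The stated conditions are a two-sided 5% test, "assuming 20% drop out in order to have at least 80% power to detect a 2 kg difference in weight gain/retention between intervention arms". The 2 kg is taken from an earlier trial's effect on gestational weight gain. The same section adds that a difference of 0.45 (SD 1.0) in a z-score for birthweight or for infant BMI is detectable with 80% power at this sample size.
- **Outcomes:** "Our primary outcome will be body composition measured through body mass index (BMI) of the family members", with the bracketed detail "self-reported, the mother’s, if available father’s and the child’s height and weight".

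The Background gives the expected effect as "indicated by a body mass index (BMI) that is more stable than in the control condition", and the Abstract speaks of weight gain in the parents. By Table 2 (Austria), parental weight is collected after baseline at t0.5, t1 and t2, and the child is measured at t1 and t2. By Table 3 (Germany), all three persons are measured at t0, t1 and t2. The Statistical analyses section refers to the primary outcome in the singular and adjusts for the baseline value of the outcome. It names neither a person nor a visit.

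**The concern.** The primary outcome fixes which result decides the trial and what the alpha and power refer to. Here one section makes it a weight difference, apparently one value per family, and another makes it the BMI of up to three people per family. If the results differ between mother, father and child, the article gives no way to say whether the trial succeeded, and the choice could be made after seeing the data. The 5% and 80% are stated for single comparisons and are not shared out over several.

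The persons are also not interchangeable. In an adult of fixed height, kg and BMI change are proportional. In an infant whose length is changing they are not, and the sample size section itself uses a z-score for the child.

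**Working it through.** **1. The plan's own figure.** The only complete set of inputs is the child z-score statement: difference 0.45, SD 1.0, two-sided 5%, power 80%.

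- n per arm = 2 × (1.96 + 0.84)² × (1.0/0.45)² = 78 (79 with the t-test).
- With 20% dropout: 78/0.8 = 97.5, so 98 (99 with the t-test). This agrees with the planned 100 per arm, or 80 completers.
- No SD is given for the 2 kg. With 80 completers per arm, 80% power for 2 kg implies SD = 2 / [(1.96 + 0.84) × √(2/80)] ≈ 4.5 kg. I use this value below as an assumption.

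Both statements therefore reproduce as single tests, each at the full 5%.

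**2. How far kg and BMI differ.** At assumed adult heights of 1.60 and 1.70 m, 2 kg is 2/1.60² = 0.78 and 2/1.70² = 0.69 kg/m². For one adult the two measures are a rescaling, so the conflict that matters is over which person and which visit.

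**3. How many comparisons fit the Outcomes wording.** The article does not say how many tests are intended, so this is a range.

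- Smallest reading, three persons at one visit: 3 tests.
- Largest reading, every person at every follow-up visit: Germany 2 + 2 + 2 = 6; Austria 3 + 3 + 2 = 8.

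**4. Chance of at least one false positive.** This assumes each test is at 5% and any positive result counts as success. For k independent tests it is 1 − 0.95^k. The correlated column is simulated (400,000 multivariate normal draws), with assumed correlations of 0.5 to 0.9 between visits within a person and 0 to 0.2 between persons.

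| Reading | k | Independent | Correlated |
|---|---|---|---|
| Three persons, one visit | 3 | 14.3% | not simulated |
| Germany, all follow-up visits | 6 | 26.5% | 19% to 25% |
| Austria, all follow-up visits | 8 | 33.7% | 22% to 30% |

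**5. Cost of keeping three co-equal tests.** With Bonferroni (5%/3) and the assumed SD of 4.5 kg for each test, 2 kg needs 106 completers, or 106/0.8 = 132.5, so 133 recruited per arm. At the planned 80 completers, power falls from 80% to 66%. This is illustrative only, since 2 kg has no meaning for the child. Fathers take part only if present and willing (Participants), so their comparison has fewer than one value per family whenever a father does not join.

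**6. Baseline adjustment.** In Austria t0 falls in weeks 18 to 22 of pregnancy, so the child has no t0 value. The adjustment in the Statistical analyses section cannot be applied to Austrian child BMI.

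**The case against.** The strongest reply is that this is a condensed article. A primary visit, a multiplicity rule and the standardisation of child BMI are commonly left to the full protocol or the analysis plan, and neither is shown. That is right, and their absence alone would be no finding. What remains is that the article states two different primary outcomes, one of which puts three persons on an equal footing. An unseen plan could only settle this by overruling one of the two sections.

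A reader might also infer more than the text supports:

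- *That each trial is powered for one test and plans no BMI effect.* The sample size section also gives a detectable difference for an infant BMI z-score. It is a second single-test statement at the full 5%, with no joint power, but it is there.
- *That the 2 kg refers to the mother.* The section does not say so. It is a fair inference, because only the mother must take part.
- *That the Background phrase on BMI stability is a third endpoint.* It explains what is meant by preventing unhealthy gain, and its direction is clear.
- *That the plan carries a 19% to 34% error rate.* No section says that every person-by-visit comparison is tested at 5% or that one positive result suffices. A multilevel model may also use the visits jointly.
- *That adult and infant BMI will be pooled.* The reference to individuals within families can equally mean the two parents, who answer separately.
- *That alpha must be shared between the two trials.* They are registered separately and are initially analysed separately.

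**Conclusion.** The conflict between the Sample size calculation and the Outcomes section is explicit and needs to be resolved. Under the Outcomes wording there are several co-equal primary comparisons, and the stated 5% and 80% cover none of them jointly.

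The size depends on a rule that the plan does not state. If any positive person counted as success, the error rate would be up to about 14% per trial at one visit. With all follow-up visits tested as well, it would be at most about 26% in Germany and 34% in Austria, and lower under the positive correlations assumed above. The figures show what the wording leaves open and do not describe a stated analysis. The weight-versus-BMI difference matters little for an adult. It matters for the child, who in Austria also lacks the baseline value that the analysis requires.

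**What to change.** Reconcile the two sections by naming one primary person, measure and visit for each trial, before any outcome analysis.

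- **Person and measure:** the mother is the natural choice, as the only mandatory participant. Use her weight in kg, or its BMI rescaling, adjusted for t0.
- **Visit:** match it to the quantity behind the 2 kg, which comes from gestational weight gain. In Austria, t0.5 is the only post-baseline visit in pregnancy and suits gestational gain; a postpartum visit suits retention. In Germany it must be a postpartum visit, such as t1. A common t1 is not the automatic answer: it falls 8 weeks after birth in Austria and 3 to 15 months after birth in Germany.
- **Secondary:** paternal BMI, child BMI as an age- and sex-standardised z-score analysed separately from the parents, and the remaining visits.

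The cost is wording only. Alpha stays at 5%, the target stays at 100 families per arm, and no extra families are needed. The price is that father and child results no longer count as primary.
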